## Methods

### Overview

TENS with music study will be a prospective, randomized controlled pilot study to compare TENS alone to TENS combined with participant self-selected music. The participants will be randomized to receive 2 weeks of TENS therapy and 2 weeks of TENS with self-selected music using a streaming service, CD player, Long Play, or radio. The order in which this is delivered will be determined by randomization. Therefore, 1 group will receive standard TENS for 2 weeks, followed by TENS with self-selected music for 2 weeks. This order will be reversed in the other group with no washout period. The participants will be compared against themselves for the outcomes, thus reducing the number of participants to power the study. We are hoping to recruit 20 participants for this pilot trial (Figure 1). We will use TENS and TENS with music as part of a holistic pain management plan involving pain neuroscience education, behavior activation, and coping skills training that is individually tailored and not as a stand-alone intervention for pragmatic reasons.

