### Randomization

Participants will be randomized in a 1:1 ratio to 1 of 2 treatment sequences:

Sequence AB: 2 weeks of standard TENS followed by 2 weeks of TENS combined with self-selected musicSequence BA: 2 weeks of TENS combined with self-selected music followed by 2 weeks of standard TENS

Randomization will be performed using a computer-generated allocation list created in Stata (StataCorp LLC) before study commencement. A permuted block design with variable block sizes will be used to ensure balance between sequences throughout recruitment. The randomization seed and code will be archived to allow reproducibility. Allocation concealment will be maintained by storing the randomization list in the Research Electronic Data Capture (REDCap; Vanderbilt University) randomization module, which will reveal the assigned sequence only after a participant has provided informed consent and completed baseline assessments.

The randomization result will be communicated to participants by telephone within 24 hours of their initial assessment. Investigators responsible for outcome collection and statistical analysis will remain blinded to treatment sequence. Participants cannot be blinded due to the pragmatic nature of the intervention.

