### Power Calculation

Power was planned for the primary within-subject comparison (paired difference between TENS with self-selected music and TENS), with a 2-sided *α*=.05 and 80% power. In the absence of previous variance data, sensitivity analyses were conducted across standardized paired effect sizes (dz). The required numbers of completed pairs (participants who complete both study periods) are presented in Table 2.

**Table 2. T2:** Sample size calculation.

Effect size (dz)	Completed pairs needed, n	Recruits with 10% dropout, n	Recruits with 20% dropouts, n	Recruits with 30% dropouts, n
0.4	52	57	62	68
0.5	34	37	41	44
0.6	24	26	29	31
0.7	19	21	23	25
0.8	15	17	18	20

As a pilot study (target recruitment N=20), the trial is adequately powered only for larger effects (approximately dz≥0.70). Therefore, the primary purpose of this pilot study is to assess the feasibility, estimate variance, and provide effect size estimates to inform the definitive sample size for the main trial.

All calculations were performed using G*Power version 3.1 (Heinrich Heine University), which is widely used for sample size and power analysis in clinical research.

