### Statistical Methods

This study is a 2-period, 2-sequence crossover pilot trial without a washout period between treatments. Analyses will primarily focus on feasibility outcomes (recruitment, adherence, data completeness, and dropout) using descriptive statistics (means, medians, and proportions) with 95% CIs rather than formal hypothesis testing. These feasibility metrics will inform the practicality of conducting a larger definitive trial.

For the primary clinical outcome of pain intensity, exploratory analyses will first be conducted using paired *t* tests to compare mean scores between TENS and TENS with self-selected music within participants. Normality of paired differences will be assessed using graphical methods and the Shapiro-Wilk test. If assumptions are violated, the Wilcoxon signed-rank test will be applied as a nonparametric alternative. Categorical variables (eg, adverse events and compliance categories) will be analyzed initially using chi-square tests, or Fisher exact test if expected cell counts are small. All tests will be 2-sided with a significance level of *α*=.05.

Following these preliminary analyses, formal modeling tailored to the crossover design will be undertaken. Linear mixed-effects models will be specified with fixed effects for treatment (TENS vs TENS with self-selected music), period, and sequence, and a random intercept for participant to account for within-participant correlations. Because no washout period is present, carryover effects will be explicitly assessed by including a prior-treatment term and by examining period×sequence interactions. If evidence of carryover is observed, analyses will be restricted to first-period data as a sensitivity check, treating it as a parallel-group comparison.

Secondary outcomes (mood, function, satisfaction, medication use, and adverse events) will be analyzed using appropriate mixed-effects regression models: linear for continuous outcomes, cumulative logit for ordinal outcomes, negative binomial for counts, and logistic for binary outcomes. These analyses are exploratory in nature. Given the pilot design and small sample size, no formal correction for multiple testing will be applied; instead, effect sizes and CIs will be reported to guide future sample size calculations.

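### For uncommon binary events, the planned mixed logistic model will often yield no finite treatment odds ratio with about 10 people per sequence-by-period cell

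*Protocol article*

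**What the plan says.** The Statistical Methods section of the protocol article describes two layers of analysis for outcomes such as adverse events. In the preliminary layer, categorical variables, with adverse events as an example, are "analyzed initially using chi-square tests, or Fisher exact test if expected cell counts are small". The second layer is modelling suited to the crossover. For the linear case the terms are written out: "Linear mixed-effects models will be specified with fixed effects for treatment (TENS vs TENS with self-selected music), period, and sequence", plus a random intercept for participant. The secondary outcomes (mood, function, satisfaction, medication use and adverse events) then go to mixed-effects models chosen by type of outcome: "linear for continuous outcomes, cumulative logit for ordinal outcomes, negative binomial for counts, and logistic for binary outcomes". No separate list of fixed effects is given for the non-linear models. The section calls these analyses exploratory and says that effect sizes and CIs will be reported in place of multiplicity-corrected tests.

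The sample size is given under Overview ("We are hoping to recruit 20 participants for this pilot trial") and the allocation under Randomization ("Participants will be randomized in a 1:1 ratio to 1 of 2 treatment sequences"). The Outcomes section counts worsening pain and skin reaction as adverse outcomes. No expected adverse-event rate appears anywhere.

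**The concern.** A logistic model that has as many fixed-effect parameters as design cells reproduces each cell's observed proportion. When a proportion is 0 or 1 its logit is infinite, and so is any contrast that uses it. With about 10 people in a cell this happens easily for an uncommon event.

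The section promises effect sizes and CIs. For a rare adverse event, such as possibly a skin reaction, the named model may return a meaningless odds ratio with an enormous standard error, or fail to converge. What is reported in its place would then be chosen after the data are seen. Adverse events also bear on the first hypothesis, which includes tolerability.

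**Working it through.** **The plan's own figures.** The article states no figure for binary outcomes. Its completed-pair numbers in Table 2 (52, 34, 24, 19 and 15) concern the paired comparison of a continuous outcome. They reproduce exactly with a paired t test at two-sided 0.05 and 80% power, so they are not in question here.

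**Inputs.**
- 20 participants (Overview), randomized 1:1 (Randomization): 20 / 2 = 10 per sequence, hence m = 10 per sequence-by-period cell before dropout.
- Fixed effects: treatment, period and sequence, carried over from the linear model (an inference, tested below).
- Event risk p per period: not given. A range of 5% to 50% is assumed, equal in both conditions.
- Dropout: Table 2 considers 10% to 30%. m = 8 represents 20%, taken for simplicity as lost from all cells.

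**Why one cell is enough.** Constant, treatment, period and sequence are four parameters for four cells. Writing L for a cell's logit, the treatment log odds ratio is

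½ [(L(AB, period 2) − L(AB, period 1)) + (L(BA, period 1) − L(BA, period 2))].

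All four cells enter, so a cell at 0 or 1 leaves the estimate infinite or undetermined. The participant intercept does not prevent this, because the likelihood keeps rising in the separated direction whatever the intercepts are.

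**Probability.** For one cell, q = (1 − p)^m + p^m. For at least one of four independent cells, P = 1 − (1 − q)^4. At p = 10% and m = 10: 0.9^10 = 0.349; 1 − 0.349 = 0.651; 0.651^4 = 0.180; P = 0.82.

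| Risk per period | P, 10 per cell | P, 8 per cell |
|---|---|---|
| 5% | 0.97 | 0.99 |
| 10% | 0.82 | 0.90 |
| 15% | 0.58 | 0.72 |
| 20% | 0.36 | 0.52 |
| 30% | 0.11 | 0.21 |
| 50% | 0.01 | 0.03 |

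**Break-even.** P = 0.5 requires q = 1 − 0.5^(1/4) = 0.159. Ignoring the negligible p^m, p = 1 − 0.159^(1/10) = 0.168 for 10 per cell and 1 − 0.159^(1/8) = 0.205 for 8 per cell, or about 17% and 21%.

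**Correlation within participants.** Simulating with a participant intercept of SD 1, 2 and 3 changes little: 0.81, 0.78 and 0.75 at 10% risk, and 0.97, 0.96 and 0.94 at 5%.

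**A leaner model.** With treatment and period only, a linear-programming check for separation on 3,000 simulated trials per setting gave 0.71 at 5%, 0.33 at 10%, 0.12 at 15% and 0.04 at 20%. With treatment only, an empty condition needs no events among 20 people: 1 − (1 − 0.95^20)^2 = 0.59 at 5% and 1 − (1 − 0.9^20)^2 = 0.23 at 10%.

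**The case against.** **The rate is unknown.** A reader might infer that the model cannot be estimated, or that its odds ratio will usually be infinite. The article does not support that. It gives no event rate, and worsening pain over two weeks need not be rare in people with chronic low-back pain. At 30% to 50% risk the problem is uncommon. This stands, and it makes the point conditional.

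**The terms are not stated for this model.** The fixed effects are written out only for the linear models; for the rest the section asks for appropriate ones. This also stands. Carrying the terms over is the natural reading, since no other crossover specification is offered, but it is an inference. Dropping sequence lowers the figure at 10% risk from 82% to 33%. It reduces the problem without removing it.

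**Other binary outcomes.** A reader might apply the result to adherence, because the Discussion anticipates about 80% and the formula gives 36% there. That is a misapplication: adherence to TENS is a primary feasibility outcome and is summarised descriptively.

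**The plan already handles small counts, and the rest belongs in an analysis plan.** Fisher's test is indeed foreseen, and a rule for non-convergence is commonly left to the SAP. However, a standard Fisher test of event by condition treats a participant's two observations as independent and supplies no paired estimate with an interval. The point is also not a missing detail: the article names a model that, for uncommon events at this sample size, often cannot deliver the promised output.

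**The stakes are low.** The analyses are exploratory, and the feasibility criteria in the Aims are 80% consent and 80% adherence. The planning for the next trial centres on the paired effect in pain. A failed adverse-event model would change none of these. This stands and sets the severity.

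**Conclusion.** The point holds in conditional form. If treatment, period and sequence are all carried into the logistic model, and if an adverse event affects fewer than about 17% of participants per period (about 21% with 8 per cell), the model will more often than not give no finite treatment odds ratio or Wald CI. Above that rate failure is the less likely outcome, and by 50% it is about 1% with 10 per cell. With treatment and period alone it remains likely at 5% risk (71%) and material at 10% (33%).

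These figures assume equal risk in both conditions, equal cell sizes and, for the formula, independent cells; the last assumption matters little. It is a minor weakness of an exploratory analysis. It leaves the linear models for pain, mood and function, and the feasibility decision, untouched.

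**What to change.** In Statistical Methods, take binary adverse-event outcomes out of the unpenalised mixed logistic model and state instead:
- the number and percentage of participants with the event in each condition, among all participants observed in that condition;
- among those observed in both periods, the paired risk difference with a 95% score-type CI for paired proportions (Newcombe or Tango);
- if a period-adjusted comparison is wanted, a Firth-penalised logistic model that respects the pairing, or the exact Mainland-Gart test.

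The cost is a sentence or two of analysis wording, best settled before the data are examined, as recruitment has begun. There are two downsides. The paired risk difference is not adjusted for period. It also omits participants who leave after the first period, whom the plan wanted to keep by using mixed models; they still count in the percentages by condition.

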### Aims

The primary aim of this study is to test the feasibility of a clinical trial comparing TENS alone to TENS combined with listening to self-selected music in participants with low-back pain with or without leg pain lasting more than 3 months. The results of this feasibility study will be used to inform a larger trial of these interventions in participants with persistent neck and low-back pain lasting more than 3 months. A larger study will be considered feasible if 80% or more of the eligible population consents to the study and 80% or more of the participants are able to adhere to the protocol. The secondary aims are to explore if combining the 2 modalities has a synergistic effect on analgesia and function. A difference of 2 points in the numerical rating scale for pain intensity will be considered significant.

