### Outcomes

The primary outcome will be the feasibility of the intervention, measured as adherence rate, dropout rate, and the percentage of the eligible population that consented. Adherence rates will include the number of participants using TENS alone or TENS with music regularly more than once per week, adherence to filling out the pain diaries and other patient-reported outcome measures, and attendance at follow-up clinic visits.

Secondary outcomes include the following:

Pain intensity as a numerical rating scale (NRS) score collected before and after each session using a pain diary. The baseline pain will be collected for 1 week before the intervention when they initially attend the clinic.Opioid and other analgesic consumption over a 24-hour period collected in the pain diaryParticipant satisfaction using a 5-point Likert scaleMood measured through the 21-item Depression, Anxiety, and Stress ScaleFunction measured through the Patient-Specific Functional Scale [14]Compliance with other interventions, such as participation in interdisciplinary pain programsAdverse outcomes, including worsening pain and skin reaction to the electrodes used in TENS

All reported adverse reactions will also be collected through the study period when using the TENS machines through entries in the pain diary as well as during interviews with the participants. The self-reported outcome measures, such as the 21-item Depression, Anxiety, and Stress Scale and the Patient-Specific Functional Scale, will be recorded through REDCap forms during the clinic appointments. Figure 2 summarizes the process.

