### Data Collection

A standardized pain diary (Multimedia Appendix 1) will be used for collecting the primary outcome and some of the secondary outcomes, such as medication taken over 24 hours. Specific forms will be used for other secondary outcomes, which are available through REDCap. The data will be stored in a password-protected, secure database via REDCap. The data collected will be deidentified and assigned a study code. The pain management unit will be the custodian of the data stored in the password-protected drive within the local health district computer, with access restricted to the investigators only. The data will be stored for 7 years after the completion of the study. Table 1 summarizes the data collection points.

**Table 1. T1:** Data collection points.

Measure	Frequency	Collection points
Pain diaries	Daily	Baseline, week 1, week 2, week 3, and week 4
Average pain over 24 hours (numerical rating scale)	Weekly	Baseline, week 1, week 2, week 3, and week 4
Medications	Weekly	Baseline, week 1, week 2, week 3, and week 4
Patient-Specific Functional Scale	Fortnightly	Baseline, week 2, and week 4
21-item Depression, Anxiety, and Stress Scale	Fortnightly	Baseline, week 2, and week 4
Pain sites update	1 time	Baseline
Pain duration	1 time	Baseline
Demographics	1 time	Baseline

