Intention-to-treat principles will be followed, analyzing participants according to their randomized sequence regardless of adherence or protocol deviations. Mixed-effects models allow inclusion of all available data, including partial data from participants who drop out after the first period, thereby minimizing bias. Per-protocol analyses will be conducted as sensitivity checks. Missing data will be handled descriptively, with analyses restricted to available cases. No multiple imputation will be attempted due to the small sample size.

As a feasibility study with 20 participants, the trial is powered only to detect large effects (approximately dz≥0.70). The observed variance and effect sizes will be used to refine sample size calculations for the definitive trial.

All analyses will be conducted using Stata and SPSS Statistics (IBM Corp).

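### The available-case rule conflicts with the protocol's own definition of adherence, so the feasibility decision can turn on which denominator is used

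*Protocol article*

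**What the plan says.** The protocol article's Outcomes section defines the primary outcome, feasibility, as "measured as adherence rate, dropout rate, and the percentage of the eligible population that consented". It then builds adherence from several parts: the "number of participants using TENS alone or TENS with music regularly more than once per week", completion of the pain diaries and other patient-reported measures, and attendance at follow-up visits.

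Aims sets the progression rule with two conditions. On consent, it requires that "80% or more of the eligible population consents to the study". On adherence, the requirement is that "80% or more of the participants are able to adhere to the protocol". The Discussion (Anticipated Findings) repeats the 80% figure for adherence. Neither place gives a limit for dropout.

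Treatment says that the daily duration of TENS is recorded in a participant diary. Data Collection says that the standardised diary "will be used for collecting the primary outcome and some of the secondary outcomes". Limitations adds that there is no concurrent electronic monitoring.

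Statistical Methods makes the feasibility outcomes the main focus of the analysis, described with proportions and 95% CIs. The same section later gives the only missing-data rule: "Missing data will be handled descriptively, with analyses restricted to available cases". That rule names no outcome to which it does not apply.

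**The concern.** For a clinical score, a missing value is a gap in the data. For adherence, it is usually the event of interest: a participant who stops, or who never returns a diary, has not adhered. The Outcomes section recognises this by making diary completion and visit attendance part of adherence. The missing-data rule, read literally, does the opposite and sets such a participant aside.

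The conflict bears on the primary conclusion. The go rule contains no dropout criterion, so the adherence proportion is the only place where losses after consent can affect the decision. If losses leave its denominator, nothing else in the rule registers them. If they stay in and count as failures, the adherence criterion also controls retention. The article does not say which applies, so the choice could be made after the data are seen.

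**Working it through.** **Inputs.** Planned size: "target recruitment N=20" (Power Calculation). Threshold: 80% adherent (Aims). Dropout of 10%, 20% and 30% appears in Table 2 only as sample-size scenarios; the article gives no expected dropout rate. The number of completed pairs in Table 2 can be reproduced (52, 34, 24, 19 and 15 for a paired t test), but this point does not rest on it.

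**Step 1: the sections side by side.**
- Aims: the denominator is the participants.
- Outcomes: an unfilled diary or a missed visit is itself a failure to adhere.
- Statistical Methods: analyses use available cases, with no exception.
- Treatment and Data Collection: TENS use is known from the diary, so a participant with no diary has no data on that component.

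The first two keep a lost participant in the denominator as a failure. The last two, taken together and literally, remove that participant.

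**Step 2: the rule under each denominator.** Let k be the number lost without a returned diary and m = 20 − k. On available cases, the smallest number adherent that passes is r = 0.8 × m, rounded up. With all 20 counted, 0.8 × 20 = 16 are needed, and the most that can adhere is 20 − k.

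| Lost, k | Remaining, m | Smallest passing r | r/m | r/20 | Highest possible with all 20 counted |
|---|---|---|---|---|---|
| 0 | 20 | 16 | 80% | 80% | 20/20 = 100% |
| 4 (20%) | 16 | 13 | 81% | 65% | 16/20 = 80% |
| 5 (25%) | 15 | 12 | 80% | 60% | 15/20 = 75% |
| 6 (30%) | 14 | 12 | 86% | 60% | 14/20 = 70% |
| 7 (35%) | 13 | 11 | 85% | 55% | 13/20 = 65% |

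On available cases the rule can be met in every row. With all 20 counted it cannot be met once 5 or more are lost.

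The planned 95% CIs would not settle the matter. They are 57% to 98% for 12/14 and 36% to 81% for 12/20 (Clopper-Pearson), and both contain 80%.

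**Step 3: how often the two readings would differ.** Suppose each participant drops out independently with probability d and leaves no diary, and each remaining participant adheres with probability a. The value of a is an assumption, since the documents give none, so a range of 80% to 95% is shown.
- Available cases: the probability that Binomial(m, a) reaches r, averaged over k from Binomial(20, d).
- All randomised: the probability that Binomial(20, (1 − d)a) reaches 16.

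| d | Reading | a = 80% | 85% | 90% | 95% |
|---|---|---|---|---|---|
| 20% | Available cases | 0.55 | 0.75 | 0.91 | 0.99 |
| 20% | All randomised | 0.10 | 0.18 | 0.30 | 0.46 |
| 30% | Available cases | 0.55 | 0.74 | 0.90 | 0.98 |
| 30% | All randomised | 0.02 | 0.05 | 0.09 | 0.15 |

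On available cases the chance of passing hardly changes between 20% and 30% dropout. With all randomised counted it falls sharply.

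**The case against.** The strongest reply is that the available-case sentence was never meant for adherence. It follows the text on intention-to-treat, mixed models and per-protocol analyses and comes just before the statement that there will be no multiple imputation. That placement suggests the clinical outcomes. The feasibility outcomes have their own descriptive analysis, in which dropout and data completeness are reported as results. Visit attendance, and the scales completed in REDCap at clinic appointments, can be scored for someone who returns no diary. A person who leaves after the first period may have returned some diary data and would not automatically drop out of an available-case count. Exact denominators are also often left to a fuller document that is not shown.

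Much of this stands. A reader might infer that the go rule cannot see dropout at all, or that the adherence rate will be biased upward. The documents do not support either as a flat statement. Aims refers to the participants and Outcomes counts missing diaries and missed visits as non-adherence; on that reading the loss of 5 of 20 already fails the rule. Upward bias arises only if the available-case rule is applied to adherence, most directly to TENS use recorded in the diary.

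The reply does not remove the conflict. The missing-data rule is stated without limit, in a section that names feasibility as its main focus. This is therefore not a detail left for later but a stated rule that, taken literally, contradicts the definition of the primary outcome. The intention-to-treat sentence does not help: it assigns people to their randomised sequence and does not say how someone without data is scored. Reporting dropout with a CI makes heavy loss visible, but no criterion uses it.

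**Conclusion.** The concern holds as a conflict between sections that leaves the adherence denominator open. Its size is a possible reversal of the primary conclusion: with 6 of 20 lost and 12 adherent, adherence is 86% and passes on available cases, or 60% and fails with all randomised counted.

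This rests on three assumptions: that the available-case rule is applied to adherence, that those lost return no usable diary, and that losses of this order occur. The last is illustrative only. With no losses the two readings agree. What level of diary completion makes an individual adherent is a separate question; the working takes the number adherent as given.

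**What to change.** - **Statistical Methods:** limit the available-case rule to the clinical outcomes.
- **Aims and Outcomes:** state that the adherence proportion uses all randomised participants as its denominator, and that dropout, an unreturned diary or a missed visit counts as not adherent.
- **Aims:** state that this all-randomised criterion also serves as the retention criterion, which gives dropout a defined role in the decision. With 20 randomised it means that at most 4 losses are compatible with proceeding. A separate dropout threshold is optional.

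The cost is a few sentences and no new data. The downside is a less favourable reported adherence rate, because someone who adhered for one period and then left counts as a failure. The Results section reports 4 of 20 enrolled at submission, so the wording could have been settled well before analysis; it should be fixed before the adherence data are examined.
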